
### Plan of Analyses

#### Aim 1 Analyses

Aim 1 evaluates the effectiveness of SBIRT-A-Family compared to SBIRT-A-Standard in preventing the escalation of AOD use. AOD use is measured using the TLFB, which computes the percentage of the days of use over the past 90 days across a range of substances. Given that we expect the percentage of the days of AOD use to be highly skewed within this population identified as predominantly low risk, we will collapse outcomes on this measure onto a 4-point ordinal scale indicating the levels of AOD use as follows: *none* (0% days of use), *once per month*
*or less* (1%-3% days of use), *between once per month and once per week* (4%-14% days of use), and *once per week or more* (≥15% days of use). Aim 1 hypotheses are tested using a mixed effects logistic regression model for ordinal longitudinal outcomes [94]:

**(1)**

**(2)**

wherein (1) and (2) are jointly estimated submodels for the SBIRT-A-Standard and SBIRT-A-Family conditions, respectively. The dependent variable in each equation is the log odds (*logit*) that AOD use response *Y* for person *i* at time point *j* (*j*=1 to 5) is in category *c* (*c*=1 to *C*−1) or lower where *c* is one of the ordinal response categories created from the AOD measure. The *b*_0_*_i_* parameters in (1) and (2) are random intercepts estimating the log odds of *Y_ij_*≤*c* at initial assessment in each condition; the *b*_1_ parameters estimate the linear rate of change (ie, slope) in the log odds of *Y_ij_*≤*c* across measurement points, which are indexed by the variable *TIME_j_*. The *γ_c_* parameter estimates thresholds between adjacent categories on the given AOD variable. The intercept in each submodel is specified as a random effect to account for the nesting of repeated measurements within individuals. Slope parameters are specified as fixed effects. The model is specified as jointly estimated simultaneous equations for each study condition, rather than a single model containing an intervention main effect and interaction term, to allow for greater flexibility in modeling group-specific effects as well as for comparing each condition to the normative comparison (NC) group of youth (in which the given youth, standard condition or youth and family, family condition, screened negative). Changes in the levels of AOD use are captured by the *b*_1_ parameters in each submodel, where positive values of *b*_1_ indicate an increase in the log odds of being in a lower AOD use category on each logit over time compared to the initial assessment. The causal effect of assignment to SBIRT-A-Standard versus SBIRT-A-Family on AOD use (ie, the intent-to-treat effect) is estimated as the difference between *b*_1_*_,sbi−fam_* and *b*_1_*_,sbi_*_._ Separate models are fitted for each AOD use outcome variable. To account for nonindependence due to the clustering of individuals within clinic sites, indicator variables controlling for the fixed effect of each clinic will be included as covariates in submodels (1) and (2) [95].

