### Recruitment, Randomization, Intervention Flow, and Outcome Assessment Procedures

Study recruitment and randomization as well as all SBIRT-A activities occur on the day of the visit in PC offices. Figure 1 depicts the flow of patient recruitment, patient randomization, and SBIRT-A delivery for various risk categories. Recruitment efforts will be multimethod, consisting of (1) informational flyers in wait areas, (2) outreach to families by site research staff, and (3) warm handoff by site administrators and providers when needed. Interested caregivers are prompted to contact on-site research staff, who then give the designated caregiver a tablet to (1) complete an electronic research consent form, (2) provide family demographic and brief assessment information, and (3) complete a screening tool assessing their concerns about the adolescent’s AOD use and related behavior problems as well as family communication about AOD issues. Simultaneously, research staff give a tablet to the youth, who completes an electronic research assent form, and if their caregiver gives consent, an AOD screening tool and brief assessment information.

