Every adolescent or family assigned to an *at risk* category in either condition is enrolled until study capacity is reached (n=2000). In addition, a randomly selected subsample of adolescents (n=300; balanced across conditions) screened as *low risk* are followed for outcome assessments; the selection of the group categorized as *low risk* uses quota sampling based on sex, race, ethnicity, and age. Outcome data are collected via remote digital assessment methods at initial assessment (as soon as possible after the PC visit) and at 3, 6, 9, and 12 months after the PC visit using REDCap Cloud software (Research Electronic Data Capture developed at Vanderbilt University and licensed to cloud-based technology company nPhase, Inc), a widely used secure, Health Insurance Portability and Accountability Act (HIPAA)–compliant, web-based data collection platform. Figure 2 shows the SPIRIT (Standard Protocol Items: Recommendations for Interventional Trials) checklist depicting the schedule of trial enrollment, interventions, and assessments. All youth and caregivers separately receive both email and SMS text prompts when assessments are due, using contact information provided during the consenting process. When either youth or caregiver fails to complete a follow-up assessment, research staff members blinded to condition assignment reach out to arrange a live assessment via telephone or videoconference. Each assessment requires approximately 20 minutes to complete.

Clinicians and families enrolled in the study retain the right to withdraw consent at any time. The protocol will be discontinued at any site where procedures become burdensome or otherwise impinge on the routine performance of participating staff. Analysis of intervention impacts and potential harm will be continuous throughout the trial. In cooperation with the administration of the partnering sites, investigators will provide full study debriefing and offer counseling referrals to any participant aggrieved or injured due to trial participation.

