### Study Conditions

Both study conditions follow a similar set of procedures anchored in the use of handheld tablets. As depicted in Figure 1, tablets are used to collect screening data from youth and caregivers, calculate youth and family risk levels, and offer digitally supported BI and RT activities to users. Point-of-care digital SBIRT procedures can improve patient outcomes by facilitating more rapid and standardized services, data-informed clinical decision-making, and improved practice efficiency [16,51]. Both conditions feature 2 types of digital BIs: *patient facing* (ie, self-administered: patients navigate the BI alone on the tablet) and *provider facing* (ie, provider administered: providers and patients jointly navigate the BI on the tablet). The total time needed to deliver each approach matches the typical wait time for preventive visits plus time devoted to delivering comparable SBIRT-A procedures for youth identified as at risk in routine PC. Both conditions allow all youth and caregivers to speak with providers about AOD issues at any point they choose, in keeping with best practices honored at partner sites. When study interventions are not delivered during the main visit, providers can opt to complete interventions in a follow-up visit scheduled within 1 week or complete immediate handoff to an on-site behavioral health specialist (trained in all study procedures) to complete the intervention [21,52]. In addition, caregivers in both conditions are digitally prompted to enroll in a web-based suite of caregiver-focused resources (helpline, parent coaching, parent groups and electronic resources, and SMS text messaging) specifically designed to support youth AOD risk reduction and caregiver self-care [53].

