### Fidelity Measures

A provider self-report fidelity checklist is collected after every encounter with every family. The checklist assesses information on which the provider-facing intervention components were delivered: adolescent BNI, caregiver BNI, facilitated conversation, or RT. Checklist items feature 3-point Likert-type rating scales to indicate how clinically helpful the given component was for the encounter: *not at all*, *somewhat*, or *very*. The checklist also logs (1) which implementation scenario was selected for intervention delivery: pediatrician intervention during visit, pediatrician follow-up visit, or behavioral specialist intervention on the visit day; (2) whether the intervention occurred in person or via video call; and (3) the number of minutes spent delivering the intervention or interventions. Research indicates that clinicians can reliably self-report on the delivery of behavioral interventions with families using brief postencounter fidelity checklists [74-76]. In addition, during initial follow-up assessment, adolescents and caregivers report on which components they experienced during the encounter: psychoeducation, BNI, facilitated conversation, or RT.

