#### Aim 2 and Aim 3 Analyses

Aim 2 evaluates the comparative effectiveness of study conditions on AOD risk factors (eg, peer conduct problems, susceptibility to peer pressure, school problems, and family functioning), co-occurring problems (internalizing, externalizing, and impulsivity), quality of life, and parent-adolescent AOD communication. A similar modeling approach to aim 1 is used, the primary difference being that all outcome variables are continuous rather than ordinal; as such, standard mixed effects growth models [97] are used to compare intervention effectiveness. Aim 3 compares the rates of behavioral counseling service use between the conditions. Differences are tested at 1-year follow-up using a simple logistic regression model with a binary *yes/no* outcome variable indicating whether the youth received any counseling during the study period. Higher rates of counseling use are expected in the SBIRT-A-Family condition.

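### The Family-versus-Standard effect is defined as a slope difference starting from an assessment made after the visit, so any benefit already present there is left out and a fading one can change sign; its standard error is also too small if youths' slopes vary.

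*Protocol article*

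**What the plan says.** All references are to the protocol article.

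- **Effect.** Aim 1 Analyses: "The causal effect of assignment to SBIRT-A-Standard versus SBIRT-A-Family on AOD use (ie, the intent-to-treat effect) is estimated as the difference between" the Family slope and the Standard slope. The two submodels have separate intercepts, described as the log odds at initial assessment.
- **Random structure.** "The intercept in each submodel is specified as a random effect to account for the nesting of repeated measurements within individuals", and "Slope parameters are specified as fixed effects".
- **Time scale.** There are five time points. Evaluating Clinical Significance codes the 1-year follow-up as 4, so the initial assessment is time 0.
- **Order of events.** "Study recruitment and randomization as well as all SBIRT-A activities occur on the day of the visit in PC offices"; Study Conditions adds that "providers can opt to complete interventions in a follow-up visit scheduled within 1 week". Outcomes are then collected at "initial assessment (as soon as possible after the PC visit) and at 3, 6, 9, and 12 months after the PC visit". Fidelity Measures confirms the order: "during initial follow-up assessment, adolescents and caregivers report on which components they experienced during the encounter".
- **Other outcomes.** The Abstract names co-occurring behavior problems and parent-adolescent communication as primary alongside substance use. For these, Aim 2 and Aim 3 Analyses says "A similar modeling approach to aim 1 is used".
- **Pre-randomisation data.** Communication (youth and caregiver), the caregiver problem monitor and CRAFFT use days are collected at screening, and the tablet randomises only after screening is complete. The analysis sections do not name these values as baselines.

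**The concern.** Time 0 of the model is a post-randomisation measurement. Whatever separates the arms by then goes into the intercepts, and only later divergence counts as effect. A benefit that is complete at time 0 and holds would be scored as nothing; one that is present at time 0 and fades would be scored as favouring Standard.

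This matters most for communication. In the named substance use category, the Family arm gives the caregiver interview and the facilitated conversation at the visit, and both address how parent and youth talk about substances. An early shift is what those components aim for.

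The second issue is precision. If youths differ in their own rates of change, or if correlation falls with the time between measurements, a model with a random intercept and fixed slopes treats that variation as independent noise and understates the standard error of the slope difference.

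**Working it through.** **1. The plan's own figure.** Inputs from Study Power: 1600 youth (800 per arm, assuming 1:1 allocation), five measurements, no alcohol use 62.3% in both arms at the start and 78.4% (Family) versus 67.9% (Standard) at 12 months, correlation 0.90, stated power 0.99. A random-intercept logistic model was fitted to 1000 simulated data sets. The outcome was simplified to none/any because only the none proportions are given, and the site correlation of 0.02 was left out. Slope-test power was 1.00, so the stated figure is reproduced. It assumes equal starting levels and linear divergence, the pattern a slope test suits best. The direct 12-month comparison of 78.4% with 67.9% has power 0.997.

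**2. Continuous outcome, benefit already present at time 0.** Assumed: n = 800 per arm, within-person correlation ρ = 0.5-0.7, SD 1, times 0 to 4 (sum of squared deviations 10).

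- Slope-difference SE = √[2(1−ρ)/(10n)] = √(1/8000) = 0.0112 at ρ = 0.5, and √(0.6/8000) = 0.0087 at ρ = 0.7.
- Lasting 0.20 SD: slope difference 0, so rejection is 5% (2.5% each way). The baseline-adjusted 12-month contrast has SE √[2(1−ρ²)/n] = 0.0433 or 0.0357, so z = 4.62 or 5.60 and power is above 0.99.
- Fading from 0.30 to 0.15 SD: slope difference −0.15/4 = −0.0375, so z = −3.35 or −4.33. The probability of a significant result for Standard is 0.92 or 0.99, although Family is still better at 12 months.

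**3. Substance use, where the 90-day look-back matters.** For a step benefit and a lag of L days, a fraction L/90 is already in the first measurement. The least-squares slope over four steps then recovers 0.8 × (1 − L/90) of the effect: 0.80 at L = 0 and 0.8 × 76/90 = 0.68 at L = 14. Simulation used the model of step 1, a peak log odds ratio of 1.289 − 0.749 = 0.54 from the plan's 12-month rates, and 300 data sets per row:

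| Pattern of benefit | Slope test | 12-month contrast, for Family |
|---|---|---|
| Lasting, none of it at time 0 | 100% for Family | 99.7% |
| Lasting, 14/90 at time 0 | 99.7% for Family | 100% |
| Lasting, all of it at time 0 | 1.7% for Family | 99.3% |
| Fades to half, none at time 0 | 52% for Family | 67% |
| Fades to half, all at time 0 | 94% for Standard | 70% |
| Fades to zero, none at time 0 | 39% for Standard | 3.3% (no true difference) |

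**4. Standard error.** Let r = 10 × var(slope)/var(residual). The true variance of a youth's fitted slope is proportional to 1 + r, while the random-intercept model reports 1 + 0.25r. Slope reliability is r/(1+r).

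- Reliability 0.2: r = 0.25, variance ratio 1.25/1.0625 = 1.18, type I error 7%.
- Reliability 0.75: r = 3, variance ratio 4/1.75 = 2.29, type I error just under 20%.

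For binary substance use under the null (600 data sets each):

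| Correlation structure | Model SE vs empirical SD | Type I error |
|---|---|---|
| Constant 0.90 | 0.062 vs 0.062 | 3.8% |
| Random slopes, initial-to-12-month correlation 0.84 | 0.060 vs 0.069 | 8.0% |
| Random slopes, 0.78 | 0.058 vs 0.073 | 10.2% |
| Random slopes, 0.67 | 0.056 vs 0.075 | 15.7% |
| AR(1) 0.9 / 0.8 / 0.7 | 21-27% too small | 14.9% / 11.0% / 11.0% |

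**5. Does the obvious remedy work here?** At-risk status uses youth data only in Standard, and youth plus caregiver data in Family. Under the null, with assumed prevalences and correlations, a 12-month contrast adjusted only for the outcome's screening value rejected in 7-35% of simulated trials. Adding the screening variables that define risk in either arm brought this to about 5-6%.

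**The case against.** - **The section quoted concerns substance use over the past 90 days.** A prompt initial assessment mostly records use before the visit. This stands. A reader might infer that an early lasting benefit on substance use counts as zero; that needs the whole benefit to be in the first measurement, which the look-back makes unlikely. What remains is that no maximum lag is set, and that even a clean starting value recovers about 80% of a step effect.
- **Aim 1 is about preventing escalation, which is a trajectory question.** A slope does address that. But the protocol calls the slope difference the intent-to-treat effect, and it omits part of what assignment does.
- **Delivery is not confined to one moment, and not everyone gets the caregiver components.** Delivery may fall within a week, caregivers in both arms are offered continuing resources, and the caregiver interview and facilitated conversation reach only the named substance use category. This dilutes the average early shift in communication without removing it. Outcomes such as peer use or school record can hardly move within days.
- **The standard errors are right under the protocol's own assumption.** Correct: with constant correlation 0.90 there is no inflation. A reader might infer that they are too small as a matter of fact; the documents give no slope variance or correlation decay that would show it. The Aim 2 text also says only that the approach is similar, so fixed slopes there are an extrapolation.
- **Arm-specific intercepts protect against a level difference built in by risk classification.** This is the strongest point. It rules out a forced common intercept, but not a 12-month contrast with the right covariates.

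**Conclusion.** The point holds in conditional form. The declared effect leaves out any arm difference present at a post-visit assessment, and the analysis sections give the pre-randomisation values no baseline role. With the benefit fully present at time 0, the slope test rejects at the null rate for a lasting 0.20 SD benefit and favours Standard with probability 0.92-0.99 for one fading from 0.30 to 0.15 SD. Those effect sizes, their timing and the 0.5-0.7 correlation are assumptions, and they bear mainly on communication. For substance use with a prompt assessment the loss is partial, and partial fading from a clean start shows as a reduced benefit rather than as harm.

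Type I error of about 7-20% rests on assumed slope variation or correlation decay, which is plausible over a year of adolescence but is not given in the documents.

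The stated power of 0.99 should not be read as wrong: it is reproduced on its own inputs, and those inputs exclude the patterns at issue. Equations (3) and (4) do use intercept plus four times the slope, but only to compare each arm with the normative group, so they do not repair the Family-versus-Standard contrast.

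**What to change.** 1. Define the Family-versus-Standard effect as the model-based arm difference at 12 months, from a model with arm by categorical time. Report the initial, 3-, 6- and 9-month differences as supportive.
2. Adjust for the pre-randomisation screening value where one exists: communication and the problem monitor for their own outcomes, CRAFFT use days for the timeline followback outcomes.
3. Do not force a common intercept. Also adjust for the screening variables that set the risk category in either arm (youth-reported use and riding risk, caregiver-reported use, problem monitor), or compare families who are at risk under one rule applied to both arms.
4. If a slope contrast is kept, add a random slope or use an unstructured or robust covariance.

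Cost: analysis-plan wording and slightly heavier model fitting, with no new data. Standard errors will be larger where slopes vary. Applying one risk rule to both arms, if that option is chosen, would change which enrolled families enter the comparison.

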#### Evaluating Clinical Significance

The clinical significance of intervention effects on youth AOD use at 1-year follow-up is evaluated by gauging the degree to which youth identified as at risk resemble youth in the NC group, which provides a normative benchmark against which to compare changes in AOD use in the 2 study conditions. Analyses are performed by adding a third submodel to those shown in (1) and (2) that estimates change in AOD use levels between initial assessment and 1-year follow-up among NC youth. By definition, 100% of NC youth are in the *none* AOD use category at initial assessment. On the basis of preliminary analyses using data from the NSDUH, this percentage is expected to decline to approximately 90% at 1-year follow-up, whereas increases are expected in both study conditions. The difference in the likelihood (ie, log odds) of reporting AOD use in the *none* category at 1-year follow-up in each study condition compared to the NC group is quantified in the following equations:

NC versus SBIRT-A-Standard: [(*b*_0_*_i_*_,_*_no−risk_* + *b*_1,_*_no−risk_* × 4 + *γ*_1_) – (*b*_0_*_i_*_,_*_sbi_* + *b*_1,_*_sbi_* × 4 + *γ*_1_)] **(3)**

NC versus SBIRT-A-Family: [(*b*_0_*_i_*_,_*_no−risk_* + *b*_1,_*_no−risk_* × 4 + *γ*_1_) – (*b*_0_*_i_*_,_*_sbi−fam_* + *b*_1,_*_sbi−fam_* × 4 + *γ*_1_)] **(4)**

where *b*_0_*_i_*_,_*_no−risk_* and *b*_1,_*_no−risk_* are the intercept and slope parameters in the mixed effects longitudinal logistic regression submodel for the group, *4* is the coded value for *TIME_j_* at 1-year follow-up, and *γ*_1_ is the threshold for the *none* category on AOD use variable *Y*. A log odds value of 0 resulting from the aforementioned differences indicates equivalence between the groups, whereas positive log odds values indicate a higher likelihood of reporting *none* at 1-year follow-up in the NC group. These differences are converted into odds ratios and then into Cohen *d* values using an “odds ratio to *d*” conversion formula [96]. The Cohen *d* value between the NC and SBIRT-A-Family groups is expected to be in the *small* range (0.10-0.30), and the Cohen *d* value for the NC versus SBIRT-A-Standard comparison is expected to be in the *moderate* range (0.40-0.60). Small effect size values would indicate high concordance in AOD use between the NC group and the at-risk study categories, thereby supporting the clinical significance of intervention effects at 1-year follow-up.

#### Aim 2 and Aim 3 Analyses

Aim 2 evaluates the comparative effectiveness of study conditions on AOD risk factors (eg, peer conduct problems, susceptibility to peer pressure, school problems, and family functioning), co-occurring problems (internalizing, externalizing, and impulsivity), quality of life, and parent-adolescent AOD communication. A similar modeling approach to aim 1 is used, the primary difference being that all outcome variables are continuous rather than ordinal; as such, standard mixed effects growth models [97] are used to compare intervention effectiveness. Aim 3 compares the rates of behavioral counseling service use between the conditions. Differences are tested at 1-year follow-up using a simple logistic regression model with a binary *yes/no* outcome variable indicating whether the youth received any counseling during the study period. Higher rates of counseling use are expected in the SBIRT-A-Family condition.

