### Specific Aims of the Randomized Effectiveness Trial

This randomized effectiveness trial will advance research on SBIRT-A in PC by conducting a head-to-head test of 2 conceptually grounded, evidence-informed approaches: a standard adolescent-only approach (SBIRT-A-Standard) versus a more expansive family-based approach (SBIRT-A-Family). The SBIRT-A-Family approach enhances the procedures of the SBIRT-A-Standard approach by screening for AOD risk with both adolescents and caregivers; leveraging multidomain, multireporter AOD risk and protection data to inform case identification and risk categorization; and directly involving caregivers in BI and RT activities [43]. The trial will test the effectiveness of SBIRT-A-Standard versus SBIRT-A-Family for preventing the escalation of AOD use (aim 1); reducing AOD use risk factors and consequences, decreasing co-occurring behavior problems, enhancing parent-adolescent communication about AOD use, and increasing quality-of-life indicators (aim 2); linking youth and families to behavior counseling services (aim 3); and investigating the extent to which the effects of SBIRT-A-Family vary based on youth characteristics (age, sex, and race or ethnicity) and youth AOD risk status (aim 4).

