## Methods

### Trial Design

This trial uses a 2-arm parallel-group multisite randomized effectiveness design. The 2 SBIRT-A approaches (SBIRT-A-Standard and SBIRT-A-Family) both use digitally supported BIs [16,49] that are a substantial upgrade over routine practice and consistent with the recommendations of the American Academy of Pediatrics to leverage digital tools. Individual youth and their caregivers are randomized as a family unit to the study condition. Adolescent and family outcomes for 2300 youth (n=2000, 86.96% identified as at risk of AOD use and n=300, 13.04% as a developmental comparison identified as low risk) are assessed over 1-year follow-up.

The protocol was developed according to the SPIRIT (Standard Protocol Items: Recommendations for Interventional Trials) 2013 statement (Multimedia Appendix 1).

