#### Study Patients and Inclusion Criteria

The study enrolls adolescents and their caregivers attending a PC visit at 1 of the 3 study sites. The study inclusion criteria are as follows: youth aged 12 to 17 years; a primary caregiver (ie, parental figure) also in attendance; youth is fluent in English, and caregiver is fluent in English or Spanish; both are capable of using audio-assisted informed consent procedures and independently operating a handheld tablet; and both complete routine site AOD risk screening questions prompted during PC visit intake. On the basis of existing patient flow at each site, we have projected aggregate self-reported demographic characteristics of enrolled youth (Table 1).

This profile supports planned moderator analyses for sex, race, ethnicity, and age subgroups. The randomization procedures will (1) block and stratify by clinic site and (2) use imbalance minimization procedures for adolescent age (12-14 y vs 15-17 y) and study clinician.

**Table 1 table1:** Projected aggregate self-reported demographic characteristics of enrolled youth (N=2000).

Demographic characteristics			Participants, n (%)

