
### Outcome Measures: Follow-Up Interviews

The timeline followback (TLFB) method [83] is the gold standard method for collecting youth report retrospective estimates of AOD use using a calendar visual aid to facilitate recall. This study used a computer-administered and calendar-assisted instrument created for REDCap-compatible remote asynchronous follow-up assessment modeled after the TLFB [31]. This version assesses the number of days that youth used alcohol, tobacco, marijuana, non–medical prescription drugs, inhalants or vapes, and herbs or synthetic drugs over the past 90 days. If alcohol was used, follow-up questions assess binge drinking episodes. The KIDSCREEN-27 questionnaire (youth and caregiver report) [84] measures youth functioning in social and school domains. Items assess the degree to which youth have experienced problems with a specific task or activity during the past month. It is internationally used and has excellent psychometric properties with strong construct validity and test-retest reliability [84,85]. The Services Assessment for Children and Adolescents (caregiver report) [86] assesses the youth’s past and current use of inpatient, outpatient, and school-based behavioral health services. It has shown strong validity and test-retest reliability [87] as well as interrater reliability between parent and child reports [88]. Items were added to assess caregiver enrollment and the use of web-based educational and support resources for adolescent AOD. Perceived Risk (youth report) [89] asks youth to rate the degree to which people risk harming themselves if they use various categories of substances on a 4-point scale ranging from *no risk* to *great risk*. Peer Deviance (youth report) [89] assesses the number of peers who use various substances on a 5-point scale ranging from *none* to *all*. Parent Rules about Substance Use (youth and caregiver report) [90] assesses parent rules about using various substances on a 6-point scale ranging from *not allowed to use AOD* to *no rules about using AOD*. The Family Assessment Device (youth and caregiver report) [91] assesses family relationships, communication, and problem-solving on a 4-point scale ranging from *strongly agree* to *strongly disagree*. The Comprehensive Adolescent Severity Inventory (youth report) [92] assesses academic achievement, school connection, and disciplinary record. Youth-Provider Connectedness (youth report) [93] assesses the level of trust and connection adolescents feel toward their health care providers on a 5-point scale ranging from *not at all* to *very much*. Psychoeducation Knowledge (caregiver report; created for this study) assesses caregiver knowledge of the tablet-delivered AOD psychoeducation. The Parent-Adolescent AOD Communication Frequency measure, Parent-Adolescent AOD Communication Quality measure, and Brief Problem Monitor (all described in the previous subsection) are also administered at follow-up to youth and caregivers.

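### Aim 3 is framed as linkage, but its outcome counts counseling already under way at the visit, which attenuates a true linkage effect and lowers power

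*Protocol article*

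**What the plan says.** The Specific Aims section describes the third aim as "linking youth and families to behavior counseling services (aim 3"). The referral-to-treatment procedures in both arms fit that framing: the provider recommends counseling and helps arrange a first appointment for those who agree.

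The section Aim 2 and Aim 3 Analyses words the comparison differently: "Aim 3 compares the rates of behavioral counseling service use between the conditions". The outcome, coded yes or no, is an "outcome variable indicating whether the youth received any counseling during the study period". The model is a simple logistic regression applied at one year, and no covariate for counseling at entry is named. The expected direction is stated, "Higher rates of counseling use are expected in the SBIRT-A-Family condition", but no rates are given.

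On entry, "The study enrolls adolescents and their caregivers attending a PC visit at 1 of the 3 study sites", and none of the listed criteria concerns counseling already under way. Neither the stratification nor the balancing factors include it. The service-use measure is a caregiver report of the youth's "past and current use of inpatient, outpatient, and school-based behavioral health services".

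On allocation, "Individual youth and their caregivers are randomized as a family unit to the study condition". Risk category is then computed from youth data alone in SBIRT-A-Standard and from youth plus caregiver data in SBIRT-A-Family. In the Family arm, a clinical-level mental health score reported by the caregiver is enough to class a family as at risk.

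**The concern.** Linkage, as the referral procedures describe it, is something that begins after the visit. The outcome as fixed does not separate a start from a continuation. A youth who already sees a school or outpatient counselor and attends once more scores yes whatever happened in the clinic. The stated model has nothing to absorb this: unlike the Aim 1 and Aim 2 growth models, a single yes/no outcome carries no initial level.

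Two things are at stake. The first is dilution: youth already in care add the same number of yes answers to both arms, so the difference shrinks and the odds ratio moves toward 1. The second is possible bias, if the share already in care differs between the at-risk groups that are compared. The Family-only mental health route into the at-risk sample is a plausible way for that to happen, and it would push the result in the direction the protocol predicts.

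**Working it through.** **The plan's own figure.** The Study Power section expects power above 0.95 for Aims 2 and 3, on the ground that these outcomes are continuous. The Aim 3 outcome is binary and no counseling rates are given, so the figure cannot be reproduced. At 800 per arm, 0.95 power needs a difference of about 4.7 percentage points at a 5% control rate, 6.1 at 10%, 7.7 at 20% and 8.55 at 30%.

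**Inputs.** From the protocol: 2000 at-risk youth and 20% attrition, so 2000 × 0.80 = 1600. Assumed: 800 per arm; two-sided 0.05; new linkage p of 10% (Standard) and 15% (Family) among youth not in care; share c already in care and continuing of 10%, 20% or 30%. The protocol gives neither p nor c.

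**Formulas.** Any-counseling rate = c + (1 − c)p, so the arm difference is multiplied by (1 − c). Power = Φ((d − 1.96·SE0)/SE1), with SE0 pooled and SE1 unpooled.

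**Worked case, c = 20%.**
- Any counseling: 0.20 + 0.80 × 0.10 = 0.28 and 0.20 + 0.80 × 0.15 = 0.32, so d = 0.04. SE0 = √(2 × 0.30 × 0.70/800) = 0.0229 and SE1 = √((0.28 × 0.72 + 0.32 × 0.68)/800) = 0.0229. Power = 0.42.
- New starts: 800 × 0.80 = 640 per arm, 0.10 versus 0.15, SE0 = √(2 × 0.125 × 0.875/640) = 0.0185. Power = 0.77.

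| Already in care | Any counseling | Odds ratio | Power | New starts, n per arm | Odds ratio | Power |
|---|---|---|---|---|---|---|
| 10% | 19.0% vs 23.5% | 1.31 | 0.60 | 720 | 1.59 | 0.82 |
| 20% | 28.0% vs 32.0% | 1.21 | 0.42 | 640 | 1.59 | 0.77 |
| 30% | 37.0% vs 40.5% | 1.16 | 0.30 | 560 | 1.59 | 0.72 |

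With a larger assumed effect, 10% versus 18%, the pattern is the same but milder: 0.93, 0.79 and 0.63 for any counseling against 0.99, 0.985 and 0.97 for new starts.

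**Adjustment with everyone retained.** Simulation at 10% versus 15%, 20% in care and 85% of those continuing gave power of about 0.47 unadjusted, 0.68 adjusted for counseling at entry, and 0.78 for new starts. A repeat with 2000 replicates gave 0.45, 0.65 and 0.76.

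**Validity when prior care is equal.** With c and p the same in both arms, the observed rates are equal and the test rejects 5% of the time.

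**When prior care is unequal.** Take no linkage effect (10% in both arms), with 20% in care in Standard and 25% in Family. The rates are 0.20 + 0.80 × 0.10 = 0.280 and 0.25 + 0.75 × 0.10 = 0.325, and the test rejects about 50% of the time. At 15% versus 20% it rejects about 54% of the time.

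**Whether a new-start endpoint removes that bias.** Suppose no intervention effect, 10% new starts in general and 20% among youth who enter through the mental health route, who make up 30% of the Family arm. The Family rate is 0.70 × 0.10 + 0.30 × 0.20 = 0.13 against 0.10. With 600 Family and 640 Standard youth not in care, the new-start test rejects about 38% of the time. It does not remove the bias.

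**The case against.** The strongest reply is that a reader might infer from the dilution that the trial cannot isolate linkage caused by the intervention. The documents do not support that. Families are randomized and the test compares the arms; with equal prior care, any difference is caused by assignment and type I error holds. Dilution costs power, not validity. That stands.

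A reader might also take the 50% false-positive figure as a property of the endpoint. It is not. It needs unequal prior care, and the likely source is the arm-specific at-risk classification, which affects every at-risk comparison. That mental health entrants are more often in counseling already is an inference, not a figure in the protocol. This stands too, and is why the endpoint change alone is not enough.

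Third, service use over a year is a legitimate outcome, and the abstract calls it therapy attendance. Youth in school-based or mental health counseling could be newly linked to substance use counseling, or kept in care, and restricting the primary analysis to youth not in care would discard them. Entry status would also be reported after randomization. These points stand against restriction, not against adjustment with everyone retained.

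Finally, covariates and item coding are often left to the analysis plan, which is not shown. That carries less weight: the article itself fixes the outcome and names the model, and the outcome so fixed does not match the aim.

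**Conclusion.** The point holds as a mismatch between aim and endpoint that attenuates the effect. As written, Aim 3 measures counseling use rather than linkage. Under the assumed rates of 10% versus 15% with 10% to 30% already in care, power falls from 0.86 with nobody in care to between 0.60 and 0.30, while a new-start outcome keeps 0.82 to 0.72. The size depends on rates that the protocol does not give. The working also assumes that every youth in care continues; the simulation relaxes this to 85%, and the ordering is unchanged.

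Bias is conditional. It arises only if prior care differs between the at-risk groups, which the classification rules make possible but do not establish. The matter affects a secondary outcome under a named aim, can be repaired, and should be corrected before unblinded analysis.

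**What to change.** 1. Classify counseling at entry from the past and current service-use items, as reported at the initial assessment for the period before the visit.
2. Adjust the Aim 3 logistic model for that status, retaining all randomized at-risk youth.
3. Report counseling newly started after the visit as the linkage outcome, counting a new service type for youth already in other care. Report any counseling alongside it.
4. Repeat the comparison in a set defined by the same screening data in both arms. Youth-reported past-year use is one candidate, since it leads to an at-risk category under either arm's rules and is collected before randomization.
5. Restate Aim 3 power for a binary outcome with stated rates.

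The cost is mainly analysis wording, with three limits. The schedule figure is not shown, so collection of the service items at the initial assessment is inferred. Entry status is retrospective and reported shortly after randomization, so its balance between arms should be shown. Data collection began in March 2024, so a sharper reference date for these items cannot reach families already assessed; for them, the existing past and current answers must serve.
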